##### Secondary study parameter(s)

All analyses of secondary study parameters will use an intention-to-treat approach, with a per-protocol approach performed as a sensitivity analysis. All point estimates will be presented according to the distribution of the data (mean/median with standard deviation (SD) / Interquartile Range (IQR)).

Count outcomes: For count outcomes like PICU transfers, readmission and unscheduled visits to healthcare providers, multilevel Poisson regression will be used.Oxygen therapy duration: To investigate differences in time on oxygen therapy between groups, multivariable linear regression will be applied.Time-to-event outcomes: For outcomes such as time to last day of cough and/or salbutamol use, time to normal activities and time to discharge, Cox proportional hazards models will estimate the treatment effect. Time-to-event data will be either interval-censored or right-censored. All models will be adjusted for hospital, age, gender, respiratory distress severity at baseline, diagnosis and smoking by parents/patients if possible.Quality of life, anxiety measures and ICHOM PROMIS scores are continuous repeated measures and will be analysed using multilevel models, with random effects accounting for multiple measurements within each individual.Exploratory subgroup analyses: These will be based on diagnosis, age and skin type, as skin type might influence the accuracy SpO2 measurement.^24^,^26^ Skin type will be recorded in the discharge questionnaire by the parent as one of the six skin types defined by Fitzpatrick.^27^

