### Study setting

The trial will be conducted in the general paediatric wards of 10 general hospitals throughout the Netherlands. All sites are listed on the study website.^13^

The study commenced on 1 December 2022. The recruitment start date was 7 September 2023. The planned recruitment end date is 30 November 2025, and the trial end-date is planned for 1 December 2026.

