#### Safety outcomes

Number of PICU admissions.Number of unscheduled readmissions and revisits to healthcare providers, as reported by parents in follow-up questionnaires and registered from patient electronic health records.Duration of symptoms, defined as time in days from admission to meeting the following criteria:Resolution of cough (less than one cough every hour), as reported by parents.Resolution of dyspnoea, as reported by parents.Cessation of scheduled salbutamol use, as reported by parents.Time in days from admission to return to normal health, as reported by parents.Time in days from admission to return to school/day care, as reported by parents.Patient quality of life during follow-up, measured by digital questionnaires at discharge, 7 days, 28 days and 90 days after discharge by EuroQol Five Dimensions Health Questionnaire Youth (EQ-5D-Y) (by patient or by parent proxy form). For ages 6 weeks to 2 years, only the EuroQol Visual Analogue Scale (EQ-VAS) is used, as this is the only tool with good clinimetric properties in this age group which can be compared with the full 6 weeks to 12 years age range.^17^ For ages 2 and 3 years, a version of the EQ-5D-Y with modified wording is used, developed in an Australian study (currently in submission) and has been translated with the help of the EuroQol offices. For ages 4–12 years, the EQ-5D-Y is used (proxy version for up to 8 years, self-complete version for 8–12 years), validated in this age group.^18 19^Parental anxiety up to 1 month after discharge, measured by digital questionnaires at discharge, 7 days and 28 days after discharge by the anxiety items on Hospital Anxiety and Depression Scale.^20^Overall paediatric health was measured by digital questionnaires of International Consortium for Health Outcome Measurement (ICHOM) Patient-Reported Outcomes Measurment Information System (PROMIS) set at discharge, 7, 28 and 90 days follow-ups.

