#### Sample size and feasibility

The sample size calculation is based on the mean time to meet all discharge criteria for the two groups. We aim to demonstrate a difference of 12 hours, determined as a relevant reduction through patient/parent interviews and supported by previous research.^8^ With a mean length of stay of 72 hours and an SD of 48 hours (based on 5 years of admissions data for respiratory distress at our hospital, Statistics Netherlands (Centraal Bureau voor Statistiek (CBS)) data on admission duration and previous research^8 9^) an alpha of 0.05 and 80% power, 251 children are to be included in both intervention and control groups. With an estimated dropout rate of 10%, the goal is to include 560 patients over the 30-month inclusion period. This is feasible, as two participating centres admit an average of 200 children aged 0–12 years with respiratory disease per year. Estimating 80% eligibility, 15% not approached and 60% willingness to participate (based on parent interviews, in-hospital data and expert estimation), and with 10 participating, centres over 30 months up to 2000 children could be included.

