#### Statistical methods

##### Primary study parameter(s)

The time to meet all discharge criteria will be presented in hours. The primary analysis will be conducted on an intention-to-treat basis. Point estimates and uncertainty will be chosen based on the distribution of the data. The difference in hours between the groups will be analysed and tested for statistical significance, adjusting for centre and age and using a multilevel linear regression model for hospitals, with diagnosis and patient clinical parameters at presentation as covariates. A 12-hour difference is deemed clinically significant. Sensitivity analysis will include a per-protocol analysis of the primary outcome. For other time-to-event parameters, a Cox proportional hazards model will be used to estimate the intervention effect.

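### One Poisson model is fixed for all count safety outcomes; for unscheduled visits its standard errors can be too small unless child-level over-dispersion is handled

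*Protocol article*

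**What the plan says.** In the protocol article, Secondary study parameter(s), three safety outcomes share one model: "For count outcomes like PICU transfers, readmission and unscheduled visits to healthcare providers, multilevel Poisson regression will be used". The section does not name the level of the random effect or the variance estimator for this model.

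The Safety outcomes section defines one of them as "Number of unscheduled readmissions and revisits to healthcare providers, as reported by parents in follow-up questionnaires and registered from patient electronic health records". That is a count, so one child can contribute several events.

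Two other places bear on what multilevel means. The primary analysis is described as "using a multilevel linear regression model for hospitals". For quality of life, anxiety and PROMIS scores, the models are multilevel "with random effects accounting for multiple measurements within each individual". Neither phrase is attached to the counts. On setting and size: "The trial will be conducted in the general paediatric wards of 10 general hospitals throughout the Netherlands", and "With an estimated dropout rate of 10%, the goal is to include 560 patients over the 30-month inclusion period". No expected visit, readmission or PICU rate appears anywhere, and no dispersion.

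**The concern.** Poisson regression sets the variance equal to the mean, given the terms in the model. Healthcare visits after a respiratory admission may well depart from that: most children may have none while a few have several. The extra variation lies between children within a hospital. A hospital intercept captures only differences between hospitals, so model-based standard errors would be too small.

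PICU transfer departs the other way. It is close to a yes/no event per child, with variance below the mean, so the same model gives errors that are slightly too large. One model therefore serves outcomes whose errors go wrong in opposite directions.

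The trial's claim is that the lower threshold shortens stay safely. For visits, an understated interval could give a false signal of harm or protection, or a bound that looks tighter than the data allow.

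**Working it through.** **The plan's own figure.** It gives none for the count outcomes, so only the trial size carries over. For a 12-hour difference, SD 48 hours, two-sided alpha 0.05 and 80% power, n per arm = 2 × (1.96 + 0.842)² × (48/12)² = 251.2. The article has 251; rounding up gives 252. Then 2 × 252 / 0.9 = 560. The sample size reproduces and does not bear on this point.

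**Inputs.** From the protocol: 560 children, 1:1 allocation, 10 hospitals. Assumed, because the document is silent: mean events per child μ, and between-child heterogeneity a (gamma-distributed, as in a negative binomial model).

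**Formulas.** Variance-to-mean ratio φ = 1 + aμ. True SE / Poisson SE = √φ. Actual coverage of a nominal 95% interval = 2Φ(1.96/√φ) − 1.

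**Counts that can recur.** The simulation used 10 hospitals with 28 children per arm each, a hospital log-SD of 0.3, no treatment effect and 1,500 runs per row.

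| μ (assumed) | a (assumed) | φ | √φ | Coverage, formula | Coverage, simulated |
|---|---|---|---|---|---|
| 0.05 | 1 | 1.05 | 1.02 | 94.4% | 95.6% |
| 0.1 | 1 | 1.1 | 1.05 | 93.8% | 94.6% |
| 0.3 | 0 | 1.0 | 1.00 | 95.0% | 95.5% |
| 0.3 | 1 | 1.3 | 1.14 | 91.4% | 91.3% |
| 0.3 | 2 | 1.6 | 1.26 | 87.9% | 86.9% |
| 0.5 | 1 | 1.5 | 1.22 | 89.0% | 88.8% |
| 0.5 | 2 | 2.0 | 1.41 | 83.4% | 81.1% |
| 1.0 | 1 | 2.0 | 1.41 | 83.4% | 83.3% |

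The two-sided error of a nominal 5% test is one minus coverage: 11% at φ = 1.5 and about 17% at φ = 2.0. With a = 0 there is no loss.

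As an illustration, take μ = 0.5, φ = 2.0, 280 per arm and an observed rate ratio of 1. The Poisson SE of the log rate ratio is √(2/(280 × 0.5)) = 0.120, giving an interval of 0.79 to 1.26. The correct SE is 0.120 × 1.414 = 0.169, giving 0.72 to 1.39.

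The result depends on φ, so a low mean does not protect under every assumption. At μ = 0.1 with a = 4, φ = 1.4 and coverage is 90.2%.

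**Outcomes close to 0/1.** Here φ = 1 − p. For p = 5%, 10% and 20%, the true SE is 0.97, 0.95 and 0.89 times the Poisson SE, and coverage is 95.6%, 96.1% and 97.2%. The interval is too wide, by little at low p.

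**The case against.** The strongest reply is that the article fixes less than the concern needs. It names a Poisson family and calls the model multilevel, but states neither the random-effect level nor the variance estimator. A child-level random effect, or a sandwich variance, would also fit those words and would deal with over-dispersion. This stands. Hospital is the likelier reading, because it is the level named for the primary model and child-level effects are spelled out only for the repeated questionnaire scores, but it remains an inference.

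Dispersion checks and fallback models are commonly left to the statistical analysis plan, which was not available. Their absence from an article is no fault. What remains is that the article commits unlike outcomes to one stated model.

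The same section says that all models will be adjusted for hospital, age, baseline severity and other factors. That sentence follows the time-to-event text, so its reach is unclear. If it covers the counts, it would absorb part of the heterogeneity and shrink the effect.

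A reader might infer that the trial's safety intervals as a whole will be too narrow. The document does not support that. It gives no rate or dispersion. PICU transfer goes the other way, as does readmission if few children return more than once. Time to recovery is assigned to Cox models. The abstract's short list of safety outcomes names recovery, readmissions and PICU admissions, not unscheduled visits, and the article states no safety margin that a wrong bound would invalidate.

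**Conclusion.** The point holds as a conditional one, mainly for unscheduled visits, and for readmissions if children are readmitted more than once. For these, Poisson standard errors can be too small unless child-level over-dispersion is handled, and a hospital random effect alone does not handle it.

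Under assumed means of 0.3 to 1 visits per child and a variance-to-mean ratio of 1.3 to 2.0, coverage falls to about 83% to 91% by formula (81% to 91% simulated). At means of 0.05 to 0.1 with a = 1 it stays near 94%, which is negligible. PICU transfer gets slightly conservative intervals.

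These figures rest on assumed rates and heterogeneity, on a hospital-level random effect with model-based errors, and on no help from covariates. It is a minor improvement to secondary safety outcomes and leaves the primary analysis and sample size untouched.

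**What to change.** State the level of the random effect in the count models, and split the outcomes by type.

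- **Unscheduled visits and readmission counts:** negative binomial regression, or Poisson regression with robust (sandwich) errors at child level, keeping hospital and age group (the stratification factors) in the model. Do not cluster the sandwich on hospital: with only 10 clusters it is unreliable.
- **Any PICU transfer, and any readmission within 28 days:** binary outcomes, each with a risk ratio and a risk difference. The 28-day window matches the participant timeline and the immediate-reporting rule for readmissions.

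The cost is a few lines in the analysis plan, with no change to recruitment or data collection. The downside is possibly wider intervals for visit counts. If over-dispersion proves absent, little is lost.

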##### Other study parameters

Patient demographics and baseline characteristics will be presented using n (%) for count and nominal data, and mean/median and SD/IQR for continuous data.

Reasons for oxygen therapy: The reasons for starting and stopping oxygen therapy are nominal data. Differences between groups will be tested using regression techniques if applicable.Patient condition: The patient’s condition at the start and stop of oxygen therapy, and at discharge, will be presented as individual parameters, standardised for age where necessary.Heart rate, respiratory rate and SpO2 are continuous data.Chest retractions are ordinal data, reporting the extent and severity (jugular, subclavicular, intercostal and subcostal).Statistical tests: Parameters will be tested for differences between the groups by appropriate statistical tests (t-test/Mann-Whitney U test/analysis of variance).

##### Statistical analysis for the economic evaluation

All statistical analyses will be conducted based on the intention-to-treat principle. Missing cost-and-effect data will be imputed using multiple imputations according to the Multivariate Imputation by Chained-Equations (MICE) algorithm. Rubin’s rules will pool the results from the different multiply imputed datasets. Linear regression analyses will estimate cost-and-effect differences between intervention and control groups, adjusting for confounders if necessary.

Incremental cost-effectiveness ratios (ICERs) will be calculated by dividing the difference in the mean total costs between treatment groups by the difference in mean effects between treatment groups. Bias-corrected and accelerated bootstrapping with 5000 replications will be used to estimate 95% CIs around the cost differences and statistical uncertainty surrounding the ICERs.

Uncertainty surrounding the ICERs will be graphically presented on cost-effectiveness planes. Additionally, cost-effectiveness acceptability curves will be estimated to show the probability that the intervention is cost-effective compared with the control, across a range of different ceiling ratios, thereby illustrating decision uncertainty.^28^

##### Study procedures

###### Monitoring

An independent data safety and monitoring board (DSMB) will monitor this trial, composed of experts in paediatrics, epidemiology and statistics. Despite the trial being classified as having negligible risk, the involvement of minors incapable of giving informed consent necessitates the DSMB’s existence. The DSMB Charter outlines the board’s composition, statement on interim analysis, stopping guidelines, conflict of interests declarations and a summary of tasks and responsibilities.

An independent monitor will conduct an on-site visit at each participating centre during the trial to review the informed consent procedure, inclusion and exclusion adherence and source data verification.

### Procedures for recording and reporting adverse events

In this low intervention trial, procedures for recording and reporting of (severe) adverse events ((S)AEs) are based on a risk-proportionate approach. They follow recommendations from the Dutch Central Committee on Research Involving Human Subjects (CCMO).

Recording AEs: All AEs reported spontaneously by the subject, his/her parent(s)/guardian(s) or observed by the investigator or his staff will be recorded up until 28 days of follow-up or until the end of the disease, whichever comes last, but no longer than full study follow-up.

Exceptions include:

Elective hospital admissions or procedures.Common symptoms of bronchiolitis, viral wheeze or lower respiratory tract infections, such as coughing, dyspnoea, rhinitis, fatigue, sleep disturbance, food intolerance and bronchodilator requirement. A selection of these events (duration of cough, duration of dyspnoea and bronchodilator use) are recorded and reported within the patient questionnaires as safety parameters.Deterioration in respiratory symptoms during admission, identified by the need for high-flow nasal cannula or CPAP, is recorded and reported within the electronic Case Report Form (e-CRF).Hospital readmissions (SAE) or reassessments (AE) are recorded and reported within the e-CRF.

Immediate reporting (within 24 hours): The following SAEs are critical to safety evaluations and require immediate reporting from the investigator to the sponsor:

PICU admissions.SAEs that result in persistent disability/incapacity or death.Other SAEs likely related to the study intervention, such as readmissions within 28 days.

Non-reporting SAEs: No reporting is required for the following (S)AEs as no causal relationship with the study procedure is expected:

AEs and SAEs occur after signing informed consent but before patient randomisation or initiation of the assigned SpO2 threshold.SAEs not part of the listed SAEs requiring reporting and not considered Suspected Unexpected Serious Adverse Reaction (SUSAR).

Follow-up on AEs: All AEs will be followed until they have been resolved or until a stable situation has been reached. Follow-up may require additional tests or medical procedures as needed and/or referral to a general physician or a medical specialist.

## Ethics and dissemination

The study will be conducted according to the principles of the Declaration of Helsinki (version 2013) and in accordance with the Medical Research Involving Human Subjects Act (WMO). It has been approved by the research ethics committee (REC) of Leiden, Den Haag, Delft (EU CT number 2023-504817-56, REC number P23.045). Any important protocol modifications will be communicated to the REC and regulators.

### Patient and public involvement

Patients and/or their representatives were involved in the design of this trial and will remain involved during all phases. They were recruited with the aid of the foundation ‘Child and Hospital’ and the Lung Foundation of the Netherlands, along with a focus group of parents and patients who were admitted to the general ward with respiratory distress of the Spaarne Gasthuis. Their input will be sought when interpreting the results and when drafting lay publications.

#### Access to data

Data will be published in accordance with ZonMw’s FAIR data standards for Open Access publication, as described in the Data Management Plan.

#### Dissemination

The results of this trial will be shared through lay publications, scientific journals and academic conferences. Authorship will follow the guidelines defined by the International Committee of Medical Journal Editors (http://www.icmje.org).

## Discussion

Safe and effective oxygen therapy in children is crucial, as both undertreatment and overtreatment can have serious consequences. However, the optimal SpO2 threshold that balances safety and effectiveness is not well established in children. The main goal of the OxyKids trial is to investigate whether an SpO2 threshold of 88%, compared with 92%, in children aged 6 weeks to 12 years admitted with respiratory distress, results in a safe reduction in length of hospital stay. It uses a pragmatic design with procedures closely resembling daily clinical practice. Together with the broad range of ages and varying diagnoses, generalisability of the findings is high and implementation is facilitated.

The open-label design of the trial introduces a risk of bias that is difficult to overcome without manipulating pulse oximeter equipment, a procedure that manufacturers did not want to facilitate. To mitigate this risk all study personnel, clinicians and nurses undergo thorough training to follow the study procedures. Additionally, to quantify any potential bias, clinical parameters such as respiratory rate, heart rate and work of breathing at start and stop of supplemental oxygen will be recorded.

Due to the pragmatic design, children in the OxyKids trial will have continuous SpO2 monitoring. As was shown previously, hypoxaemia can occur in sleep without clinical deterioration in young children with bronchiolitis.^29^ Moreover, continuous SpO2 monitoring may unnecessarily escalate treatment and prolong hospitalisation in infants with bronchiolitis.^30^ However, as the OxyKids trial compares different saturation thresholds within the current standard of care in both children with bronchiolitis and older children with other diagnoses, limiting SpO2 measurements only to awake state is not in line with the aim of the trial, even though doing so could be the better clinical practice.

A common concern with lowering SpO2 thresholds is the potential for long-term neurocognitive sequelae.^31^ Children with congenital heart disease or sleep-disordered breathing and chronic or intermittent hypoxaemia in the low 90% range also had adverse cognitive outcomes.^32^ The question remains if these results can be extrapolated to a population of otherwise healthy children with acute short-term hypoxaemia. Similar to other trials investigating the safety of lower thresholds, the OxyKids trial describes short-term follow-up. The follow-up of long-term neurocognitive outcomes poses significant challenges, including standardised assessments of neurocognitive outcome measures in varying age groups, and assessment of long-term confounders. Nonetheless, follow-up studies are warranted to address these concerns.

The OxyKids trial results are expected to significantly influence clinical practice. This trial is expected to contribute to more standardised and evidence-based guidelines and provide greater insight into optimal SpO2 thresholds in paediatric medicine.

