**Trial registration number:**

NCT06016244.

STRENGTHS AND LIMITATIONS OF THIS STUDYThis pragmatic trial and study procedures are very close to real-life practice, improving the generalisation of results and future implementation.The results of this study will enable the implementation of uniform oxygen saturation (SpO2) thresholds for nearly all children with respiratory distress due to a respiratory tract infection or viral wheezing, thanks to the broad age group and various diagnoses in the study population.Asthma patients aged 6 years and older are not included as there are safety concerns about lower SpO2 thresholds during the acute exacerbation phase.The open-label design introduces potential biases, which we will minimise by registering a fixed set of clinical parameters at oxygen start and stop to quantify potential biases, as well as a thorough training of physicians, nurses and trial staff.Safety evaluations in this study do not cover the long-term neurocognitive effects associated with either a lower or higher saturation threshold, as only short-term follow-up is described. However, follow-up studies are warranted to address the potential neurocognitive effects of lower or higher saturation thresholds in the long term.

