## Methods and analysis

### Trial design

This multicentre, open-label, randomised controlled trial with two parallel arms compares an 88% SpO2 threshold for starting and stopping supplemental oxygen (intervention group) with a 92% SpO2 threshold (control group). Data will be collected during admission and via digital questionnaires 7, 28 and 90 days after discharge (see table 1, participant timeline).

**Table 1 T1:** SPIRIT patient timeline

Time point	Enrolment	Allocation	Postallocation				
	−t_1_	0	Admission	Discharge	+7 days	+28 days	+90 days
Enrolment:							
Eligibility screen	X						
Informed consent	X						
Allocation		X					
Interventions:							
Intervention (88%)			X				
Control (92%)			X				
Assessments:							
Baseline			X	X			
Primary outcome: time to meeting all discharge criteria			X	X			
Length of stay, oxygen therapy, clinical characteristics			X	X			
PICU admission			X	X		X	
Readmissions or reassessments						X	
Recovery, duration of cough, duration of dyspnoea, time to return to school/daycare					X	X*	X*
Quality of life				X	X	X	X
Paediatric global health				X	X	X	X
Parental anxiety				X	X	X	
Cost-effectiveness			X		X		X

* Only if a patient has not recovered at +7 days time point.

PICUpaediatric intensive care unitSPIRITStandard Protocol Items: Recommendations for Interventional Trials

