### Interventions

#### Intervention group

Patients in the intervention group will receive supplemental oxygen if:

Their SpO2 levels drop below 88%, by:1%–2% for at least 15 min continuously.>2% for any amount of time.When indicated by the treating physician for clinical symptoms.

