#### Control group

Patients in the control group will receive supplemental oxygen if:

Their SpO2 levels drop below 92%, by:1%–2% for at least 15 min continuously.>2% for any amount of time.When indicated by the treating physician for clinical symptoms.

Supplemental oxygen can be administered by either a face mask or nasal cannula, following local protocols. Patients are weaned of supplemental oxygen according to local protocols and based on the randomised SpO2 threshold.

Patients transferred to a paediatric intensive care unit (PICU) will receive standard care according to local PICU protocols, including SpO2 thresholds, and will be analysed according to protocol and included in the safety analyses.

To ensure adherence to the study protocol, both nurses and physicians at each centre will be trained to follow the study protocol. Any deviations from this protocol must be documented. Study protocol adherence is monitored by the registration of start and stop times of supplemental oxygen administration, including the reasons for starting and stopping, and clinical symptoms of the patient such as respiratory rate, heart rate and work of breathing. All other care is as usual. There are no prohibited concomitant care activities, drug prescriptions or interventions.

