**Figure 1 F1:**
[figure not shown]
Informed consent flow chart.

Study initiation: Study procedures begin when at least one parent/guardian provides written informed consent and the second has given verbal consent. Written consent from the second parent/guardian will be obtained within 72 hours after inclusion. The procedure is designed to accommodate emergency situations, where one parent is often present, ensuring the intervention can start as early as possible.

Informed consent process: Adequate time is provided for the informed consent process, allowing parents/guardians to receive information, ask questions, consult with family and consider their decision. For patients already on supplemental oxygen, study enrolment must be completed within 6 hours of the start of oxygen therapy to minimise time spent on supplemental oxygen outside the study protocol. For patients not yet on supplemental oxygen, informed consent is ideally obtained before the need arises but must be completed within 6 hours after the start of oxygen therapy. Beyond this timeframe, children are no longer eligible for participation.

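### The between-arm test of the child's condition at oxygen start and stop does not quantify open-label bias, because the assigned threshold itself defines those moments

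*Protocol article*

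**What the plan says.** The trial is open label. The strengths and limitations list says the resulting biases will be minimised by staff training and by "registering a fixed set of clinical parameters at oxygen start and stop to quantify potential biases". The Discussion repeats the purpose: "to quantify any potential bias, clinical parameters such as respiratory rate, heart rate and work of breathing at start and stop of supplemental oxygen".

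The analysis of these parameters is under Other study parameters. The child's condition at oxygen start, at oxygen stop and at discharge covers heart rate, respiratory rate, SpO2 and chest retractions. The stated method is: "Parameters will be tested for differences between the groups by appropriate statistical tests (t-test/Mann-Whitney U test/analysis of variance".

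The moments at which these values are taken depend on the arm. Under Trial design, the study "compares an 88% SpO2 threshold for starting and stopping supplemental oxygen (intervention group) with a 92% SpO2 threshold (control group". The Intervention group section starts oxygen when "Their SpO2 levels drop below 88" per cent, and the Control group section when "Their SpO2 levels drop below 92" per cent. Both arms add a discretionary route: "When indicated by the treating physician for clinical symptoms".

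The record is wider than the Discussion suggests. The adherence paragraph under Control group has staff log the times of each start and stop and why each happened, and requires deviations to be documented. Other study parameters also plans a regression comparison of those reasons between the groups, if applicable.

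For a child already on oxygen, "study enrolment must be completed within 6 hours of the start of oxygen therapy" (Informed consent process), so some starts happen before allocation.

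**The concern.** A comparison can measure bias only if its result without bias is known. Here it is not. The arms are observed at moments that the allocation defines, so a difference in condition is expected when everyone follows the protocol. The children also differ. Under the lower threshold some children may not start oxygen after randomisation at all, and the Primary outcome section provides for that case. The test therefore compares two post-randomisation selections, possibly at different stages of illness.

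The matter deserves care because oxygen decisions feed the primary outcome directly: the first discharge criterion is four hours without need for supplemental oxygen. If unblinded staff give oxygen above the assigned threshold more readily in one arm, time to meeting the criteria shifts. A reader will look for the safeguard the article names, and the test described does not separate threshold effect from staff behaviour.

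**Working it through.** **Plan's own figure.** Inputs from Sample size and feasibility: difference 12 h, SD 48 h, alpha 0.05 (two-sided assumed), power 80%. n per arm = 2 × [(1.960 + 0.842) × 48 / 12]² = 251.2, against 251 stated; power at 251 per arm is 79.97%. With 10% dropout, 502 / 0.90 = 558, against 560 stated. The figures reproduce and the concern does not touch them. Below, 251 serves only as a number of records per arm.

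**SpO2 at start and stop.** The gap between the two rules is 92 − 88 = 4 points.
- Full adherence, no bias: threshold-driven starts and stops differ by about 4 points. A child whose SpO2 falls well below both thresholds would start at the same value in either arm, so the observed mean gap at start may be smaller.
- Children in the 88% arm handled as if at 92%: the difference goes to about 0.

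So a difference in SpO2 is what adherence produces, and no difference points to lost separation. Neither is a measure of bias.

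**Heart rate, respiratory rate, retractions.** The article gives no relation between these and SpO2, so a range is assumed. Let a parameter shift by b SD per SpO2 point. With full adherence, no bias and a 4-point gap, the standardised difference is 4b, and the chance of a significant test is about Φ(4b × √(251/2) − 1.96).

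| b (assumed) | 4b | Chance of p < 0.05 without bias |
|---|---|---|
| 0 | 0 | 5% |
| 0.02 | 0.08 | 14% |
| 0.05 | 0.20 | 61% |
| 0.10 | 0.40 | 99% |
| 0.20 | 0.80 | over 99.9% |

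The bias-free result thus runs from the nominal 5% to near certainty, depending on a quantity the plan does not know.

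**Starts before randomisation.** These occur under usual care in both arms. The article does not say whether they enter the comparison. If a share p of analysed starts did, a 4-point gap at start would appear as 4 × (1 − p): 3 points at p = 25%, 2 points at p = 50%. Both shares are assumptions.

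**Comparison of reasons.** Let c be the number of clinical-indication starts and t the number of threshold-driven starts in an arm. The clinical share is c / (c + t). A lower threshold reduces t, so this share can rise with c unchanged and no bias. The rate per randomised child, c / N, does not move for that reason. Even so, a start between 88% and 92% is above threshold in one arm and below it in the other. Only starts at or above 92% are above threshold in both arms.

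**Check against the child's own threshold.** With 251 records in an arm, one per child, the 95% half-width for an off-threshold share p is 1.96 × √[p(1 − p)/251]: 2.7 points at 5%, 3.7 at 10%, 4.9 at 20%. That is precise enough to be useful.

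**The case against.** The strongest reply is that the article never calls the between-arm p-value its bias measure. The strengths list and Discussion say only that parameters are recorded so that bias can be quantified; Other study parameters lists generic tests; and how one becomes the other may sit in a fuller plan. The Discussion's list also omits SpO2, the one parameter for which a by-design difference is certain. For SpO2 itself, about 4 points under adherence against about 0 under contamination is a usable check of separation.

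Much of this stands. The shift in the other signs is assumed, and at 0.02 SD per point the test would rarely be significant. The document does not say that no difference means no bias. But the article does state a purpose and does fix one analysis for these parameters, and that analysis does not serve that purpose. A check of separation is worth having, but it is not a measure of bias.

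Stronger readings are tempting and unsupported. A reader might infer that off-threshold oxygen cannot be detected, or that this is the only check. Neither is so: SpO2, reasons, times and deviations are recorded, and reasons are compared between groups. A reader might also infer that the clinical route makes all above-threshold oxygen compliant, so that the per-protocol analysis is empty. That route requires clinical symptoms, weaning is tied to the randomised threshold, and the article does not define the per-protocol set. Oxygen on clinical indication is part of both strategies, so any dilution from it belongs to the strategy effect and is not automatically bias.

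**Conclusion.** The point holds in limited form. The between-arm test of condition at oxygen start and stop is confounded with the assigned threshold and does not isolate open-label bias in either direction. The wording in the strengths list and the Discussion therefore promises more than the described analysis delivers. The needed data are collected, but no analysis described sets them against each child's own threshold.

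The one size that comes from the document is the 4-point gap between thresholds. The rejection rates rest on assumed SD-per-point values, full adherence and 251 independent records per arm; the dilution figures rest on an assumed share of pre-randomisation starts being pooled.

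It would be wrong to conclude that the primary result cannot be interpreted. Its estimate, test and sample size do not depend on these auxiliary comparisons. This is a cheap improvement that should be made before analysis.

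**What to change.** Change the analysis text as follows, using data already recorded.

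1. Classify every post-randomisation start and stop against the child's assigned threshold and the recorded reason: threshold-driven, started above threshold on clinical indication, or stop delayed above threshold. Because weaning follows local protocols, the team must write down in advance how a delayed stop is identified from the records.
2. Report these by arm per randomised child as well as per episode, allowing for episodes clustered within child.
3. Report starts before randomisation separately, as baseline.
4. Compare clinical severity between arms descriptively, and only within the same SpO2 range, for example starts at or above 92% in both arms.
5. Reword the strengths list and the Discussion so that the unadjusted between-arm test is not presented as quantifying bias.

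The cost is slightly more analysis work and a share of above-threshold starts that may look unfavourable when published. One limit remains: unblinded staff judge and record the reasons, so a biased clinical indication may still be hard to tell from a genuine one.
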